## Abstract

**Background:**

The development of efficacious, cost-effective, and widely accessible programs for the prevention of eating disorders (EDs) is crucial in order to reduce the ED-related burden of illness. Programs using dissonance-based and cognitive behavioral approaches are most effective for the selective prevention of ED. Internet-based delivery is assumed to maximize the reach and impact of preventive efforts. However, the current evidence for Internet-based ED prevention is limited. The present trial evaluates the efficacy and cost-effectiveness of two new interventions (based on dissonance theory and principles of cognitive behavioral therapy (CBT)) that are implemented as add-ons to the existing Internet-based ED prevention program ProYouth.

**Methods:**

The trial is one of five sub-projects of the German multicenter consortium ProHEAD. It is a three-arm, parallel, randomized controlled superiority trial. Participants will be randomized to (1) the online program ProYouth (active control condition) or (2) ProYouth plus a structured dissonance-based module or (3) ProYouth plus a CBT-based chat group intervention. As part of ProHEAD, a representative school-based sample of *N* = 15,000 students (≥ 12 years) will be screened for mental health problems. *N* = 309 participants at risk for ED (assessed with the Weight Concerns Scale (WCS) and the Short Evaluation of Eating Disorders (SEED)) will be included in the present trial. Online assessments will be conducted at baseline, at end of intervention (6 weeks), at 6 months follow-up, and — as part of ProHEAD — at 12 and 24 months follow-up. The primary outcome is ED-related impairment (assessed with the Child version of the Eating Disorder Examination-Questionnaire (ChEDE-Q)) at the end of the intervention. Secondary outcomes include ED-related symptomatology at follow-up, ED-related stigma, ED-related help-seeking, and acceptance of and compliance with the interventions. For the health economic evaluation data on costs of the interventions, healthcare utilization and health-related quality of life will be assessed.

**Discussion:**

This is the first study augmenting a flexible prevention approach such as ProYouth with structured evidence-based modules in order to overcome some of the key limitations in the current practice of ED prevention.

**Trial registration:**

German Clinical Trials Register (DRKS), DRKS00014679. Registered on 25 April 2018.

**Electronic supplementary material:**

The online version of this article (10.1186/s13063-018-3161-y) contains supplementary material, which is available to authorized users.

## Background

Eating disorders (EDs) such as anorexia nervosa, bulimia nervosa, and binge eating disorder are severe mental illnesses associated with a substantial burden of disease and significant healthcare costs [1, 2]. Mortality is increased in all EDs and is highest among all mental disorders in the case of anorexia nervosa. EDs mainly develop during adolescence and young adulthood [3, 4] and affect both males and females. The prevalence of full and sub-threshold EDs is estimated at 15% in young women and 3% in young men [5]. In addition, many young people report ED-related attitudes and behaviors without meeting full diagnostic criteria. EDs are associated with high psychological and physical impairment and can also affect many other areas of young people’s lives, e.g., by leading to social isolation, reduced academic and professional performances, and an overall loss of quality of life [2].

Despite significant progress in prevention and treatment research over the past decades, current healthcare may not substantially alleviate the burden related to ED at the population level due to limited efficacy, availability, and reach of evidence-based interventions [6, 7]. While effective interventions for the various forms of ED exist, only a minority of patients actually benefit and recover. A major challenge in the treatment of ED is that less than 25% of those affected by ED actually seek and receive professional help. In many cases there is a substantial delay between symptom onset and access to care, leading to an increased risk of chronicity [8]. A recent systematic review revealed that help-seeking for ED is hindered by barriers such as stigma and shame, denial of and failure to perceive the severity of illness, negative attitudes towards seeking help, lack of encouragement from others to seek help, and limited knowledge about treatment resources [9]. There is consensus that it is of great importance to develop and disseminate evidence-based, cost-effective, and widely accessible prevention and early intervention tools for EDs, especially considering their high burden of illness, their challenging treatment, and their associated costs on both individual and societal levels.

Concerning the empirical evidence of ED prevention programs, three relevant systematic reviews and meta-analyses have been conducted. Stice and colleagues analyzed efficacy trials on 51 ED prevention programs. They identified a significant reduction of at least one established ED risk factor for 26 interventions and a reduction of current or future ED symptomatology for 15 interventions [10]. Selective programs proved to be more effective than universal programs, as well as programs with interactive components compared to more didactic interventions. Furthermore, multi-session programs showed larger intervention effects than single-session programs, as well as programs conducted by external facilitators compared to interventions delivered by school personnel. Although the findings were considered overall encouraging, most significant intervention effects were small, and many studies showed major methodological flaws [10].

Two more recent systematic and meta-analytic reviews independently summarized the effects of interventions for universal, selective, and indicated prevention of ED [11, 12]. Both reviews reported that the majority of interventions focused on selective prevention. Also both reviews identified the strongest evidence base for this type of preventive effort, i.e., interventions addressing individuals at risk for the development of an ED. In particular, two approaches were associated with a significant reduction of ED-specific risk factors and ED-related impairment: dissonance-based interventions and interventions based on the principles of cognitive behavioral therapy (CBT).

However, a number of remaining challenges were identified in these reviews (of which several will be addressed in the present trial). First, the content, intensity, and delivery mode of the interventions varied substantially, and comparisons to active control conditions are scarce, so that little is known about the relative efficacy of different interventions. Second, studies mostly included female adolescents and young adults (≥ 15 years), so that more research in younger samples and males is needed. Third, there is a need for research on how to improve uptake of and compliance with ED prevention among individuals at risk. Fourth, there is limited empirical knowledge on the long-term effects, cost-effectiveness, implementation, and dissemination of evidence-based prevention programs [11].

In order to enhance the reach of preventive efforts, an increasing number of Internet-based ED prevention programs have been developed in recent years. Such programs benefit from permanent availability and accessibility independent of time and location. They are easily accessible, they may be accessed anonymously, and they enable providers to tailor content to the needs of specific target groups. Several reviews have summarized the available evidence on Internet-based interventions in the field of ED. Overall, these reviews concluded that such programs are feasible and promising tools for prevention, self-help, treatment, and relapse prevention in ED [13–17]. However, they also stated that technology-enhanced care in ED is still an understudied area, that there are few adequately powered efficacy trials (especially in the field of prevention), and that there is hardly any information on the costs of interventions and their cost-effectiveness.

One of the more widely studied Internet-based prevention programs is ProYouth, which emerged from the previous programs Essprit [18] and YoungEssprit [19]. The program comprises several components that participants may use depending on their individual needs and preferences; i.e., ProYouth is a flexible (versus structured/manualized) intervention (see subsequent sections for a description of the components). Following pilot studies on the feasibility and acceptability of the program [18, 20], its efficacy was investigated in a large high-school sample in Germany [19]. An enhanced version of the program was subsequently implemented as part of the European Union (EU)-funded ProYouth initiative in several European countries. In this context, costs associated with the maintenance of the intervention [21] as well as the cost-effectiveness of different dissemination strategies were analyzed [22]. Furthermore, there is initial evidence that ProYouth may positively impact participants’ help-seeking behavior [23]. However, research also showed that ProYouth is mainly used by severely impaired participants (i.e., a “clinical” group) and that the actual target population — participants at risk for an ED or those with sub-threshold ED symptoms — rarely use the available modules (Bauer, Kindermann, Ozer, Moessner: Dissemination of an Internet-based Program for Prevention and Early Intervention: Relationship between Access Paths, User characteristics, and Program Utilization, submitted). Thus, there is a clear need to augment the program to further engage and benefit individuals at risk for the development of an ED. Therefore, the present trial focuses on the development and evaluation of two new intervention modules as add-ons to the existing ProYouth program.

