### Participants

Male and female C&A aged 12 years or older (grades 6–13) are invited to participate in the school-based ProHEAD screening. Those who provide informed consent (student and at least one legal guardian) and complete the screening will be assigned to one of the five ProHEAD sub-projects depending on their screening results (sub-project 1: clinically relevant mental health problems [29]; sub-project 2: risk for ED; sub-project 3: risky alcohol use [30]; sub-project 4: risk for depression [31]; sub-project 5: no clinically relevant mental health problems [32]).

Eligibility criteria are checked as part of the screening procedure. Inclusion criteria for the present trial are sufficient German language skills, Internet access, a high risk for an ED (Weight Concerns Scale (WCS; score > 57 [33, 34]) or sub-threshold ED symptoms based on the Short Evaluation of Eating Disorders (SEED [35]; bingeing and/or vomiting at least once a week). Individuals are excluded if they meet criteria for clinically relevant impairment as defined for sub-project 1 of ProHEAD [29]. This means that exclusion criteria for the present trial are severe ED symptoms, indicated by a body mass index (BMI) below the 5th percentile (adjusted for age and gender) and concurrent fear of weight gain, or daily bingeing, or daily vomiting assessed with the SEED [35]. Additional exclusion criteria include current suicidality, high depressive impairment measured with the Patient Health Questionnaire-9 modified for Adolescents (PHQ-A; score > 9 [36, 37]), high alcohol consumption assessed with the Alcohol Use Disorders Identification Test (AUDIT; score ≥ 20 [38]), and clinically relevant general psychological impairment operationalized with the Strengths and Difficulties Questionnaire (SDQ Total score ≥ 20; SDQ Emotional Symptoms score > 6; SDQ Conduct Problems score > 4; SDQ Hyperactivity score > 6; SDQ Peer Relationship Problems score > 5 [39, 40]).

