### Randomization and blinding

Eligible C&A will be randomized to one of the three interventions based on an allocation sequence derived from a computerized random number generator at a 1:1:1 ratio. The allocation scheme is embedded into the ProHEAD online platform; i.e., participants are automatically assigned to one of the study arms and informed electronically about the outcome without researchers having access to the allocation scheme. Randomization will be stratified by gender. Due to the study characteristics, blinding of participants and/or online counselors is not possible because participants will be informed as to which intervention they were assigned, and counselors need to provide guidance accordingly.

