### Statistical analysis

Primary data analyses will be based on the intention-to-treat (ITT) population; i.e., all participants randomized to one of the three study conditions will be included in the primary outcome analysis. Missing data patterns will be explored. Multiple imputations will be applied to impute missing data.

Repeated measures ANOVA will be conducted (time*group interaction, alpha = 5%) to test the primary hypothesis, i.e., differences in efficacy between the interventions. For the primary outcome, only the baseline and the post assessment after 6 weeks will be considered. In case of statistically significant differences, post hoc pairwise group comparisons will be conducted (Bonferroni correction). Repeated measures ANOVA will also be conducted to determine the effect of the interventions on metric secondary outcomes. Post-intervention symptom courses will be analyzed applying mixed effects models. In order to investigate gender-specific efficacy, multifactor ANOVAs will be conducted. Fisher’s exact test will be applied to compare actual help-seeking between the groups.

For the health economic evaluation, data on the costs of interventions and efficacy will be used to determine the incremental cost-effectiveness ratio (ICER) of the interventions. The ICER will provide the additional costs in monetary terms of the respective programs to be spent for gaining an additional outcome unit. Cost-utility analyses will provide information on cost per quality-adjusted life years (QALYs) gained by the various interventions. Bootstrapping procedures will be applied to provide cost-effectiveness planes and acceptability curves.

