## Discussion

In light of the high burden of illness and the economic and social costs associated with EDs, the need for efficacious and cost-effective ED prevention programs is evident. Internet-based delivery of such programs is increasingly being recommended in order to enhance the reach and scalability of interventions. The present trial is innovative in that it combines the advantages of online intervention delivery, the flexible intervention strategy of the existing program ProYouth, and the potential of two new structured additional modules developed based on the latest evidence in ED prevention research [11, 12]. These modules incorporate a dissonance-based approach and a CBT-based approach, respectively.

The inclusion of both female and male participants and younger age groups, and the use of an active control condition and long-term follow-up assessments represent further strengths of the study. The trial largely benefits from being conducted as part of the overall ProHEAD Consortium, which will ensure recruitment of a large representative school-based sample of C&A.

Importantly, we will conduct a comprehensive health economic evaluation in addition to the efficacy study. To date, only very few studies have investigated the costs and the cost-effectiveness of ED prevention programs, and the findings so far appear to be inconsistent [53, 54]. However, health economic evaluation is key for decision-making in mental healthcare and for implementation of new interventions in healthcare routines and health insurance reimbursement schemes.

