Potential limitations and challenges of the present trial include the fact that uptake of and compliance with the interventions are unknown. Research on e-mental health in general has shown that rates of both intervention dropout and study dropout may be high in such trials, and that incomplete follow-up data often question the robustness of findings even when ITT analyses are conducted. Challenges with respect to recruitment and adherence have also been reported for ED-specific prevention efforts [55]. The inclusion of male participants in the trial also represents a challenge, as there is almost no research on ED prevention in male samples. However, given that EDs also affect boys and men, it is highly relevant to study interventions in male populations. In the present trial, the dissonance-based and CBT-based modules include specific contents for male participants. Finally, it is to note that the planned sample size will be too small to directly compare the efficacy of ProYouth-DISS and ProYouth-GROUP. Analyses on the relative efficacy will thus be explorative in nature.

In summary, we expect the present trial to make an important contribution to research in the ED field by informing us on the efficacy and cost-effectiveness of the newly developed prevention tools. In case of positive results, the nature of the interventions (e.g., the combination of automated and personalized components) and the availability of the technical infrastructure as part of the ProHEAD Consortium would allow for a broad dissemination and long-term sustainability of the interventions.

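### The gender ANOVAs have too little power for a non-significant result to say anything about boys; report baseline-adjusted estimates with intervals by gender, labelled exploratory

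*Protocol article*

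**What the plan says.** The Background lists four open challenges in eating disorder prevention, "of which several will be addressed in the present trial", without naming which. One is that samples have been mostly female and 15 or older, "so that more research in younger samples and males is needed". Participants describes the screened population as "Male and female C&A aged 12 years or older (grades 6–13"), and the Discussion presents as a strength "The inclusion of both female and male participants and younger age groups".

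Gender is built into the design. "Randomization will be stratified by gender", according to Randomization and blinding. The dissonance module has a separate male version with a different target ideal, and the chat groups are separated by gender.

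On analysis, Statistical analysis says: "In order to investigate gender-specific efficacy, multifactor ANOVAs will be conducted". The primary analysis in the same section is a repeated-measures ANOVA testing time by group on baseline and 6 weeks. I therefore read the gender analysis as the time by group by gender extension of that model; the article does not spell this out.

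The Discussion adds a caution: "The inclusion of male participants in the trial also represents a challenge, as there is almost no research on ED prevention in male samples". Its statement that the sample is too small, and the label explorative, apply only to ProYouth-DISS versus ProYouth-GROUP. Sample size calculation gives power for the global test and the pairwise comparisons. No number or share of boys is stated.

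**The concern.** Investigating gender-specific efficacy is an announced analysis with a named method. Boys receive partly different material, so a different effect in boys is plausible.

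An ANOVA of this kind yields a significance test for the interaction. If that test has little power, the usual outcome is non-significance whether or not the add-ons do anything in boys. A significant pooled result together with a non-significant gender interaction invites the conclusion that the add-ons work in both genders, even when the whole effect comes from girls. The article does not warn against this reading, and the analysis carries no exploratory label.

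**Working it through.** **Inputs.** From Sample size calculation: f = 0.15, correlation ρ = 0.1, dropout 20%, 309 randomised (103 per arm), alpha 5%. From Statistical analysis: two measurements. Completers: 309 × 0.8 = 247. The male share p is an assumption. The Background gives "The prevalence of full and sub-threshold EDs is estimated at 15% in young women and 3% in young men"; with equal numbers screened and equal uptake, p = 3/(15 + 3) = 1/6. The range shown is 5% to 50%.

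**The plan's own figure.** For the time by group test, λ = f² × N × 2/(1 − ρ) = 0.0225 × N × 2/0.9 = 0.05N, with 2 and N − 3 df. The smallest N with 90% power is 257, and 257 × 1.2 = 308.4, so 309 is reproduced. With 247 completers, λ = 12.35 and power is 0.889.

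**Effect in SD units.** With arm effects 0, d, d on change scores of variance 2(1 − ρ) = 1.8, λ = N × (2/9)d²/1.8. Setting this to 12.35 gives d² = 0.405, d = 0.64 SD.

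**Interaction test, planned effect in girls and none in boys.** λ = 0.05 × N × p(1 − p), with 2 and N − 6 df. At p = 1/6: 0.05 × 247 × 0.1389 = 1.72.

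| Share of boys | Boys completing per arm | Power | Missed |
|---|---|---|---|
| 5% | 4.1 | 0.10 | 90% |
| 10% | 8.2 | 0.14 | 86% |
| 1/6 | 13.7 | 0.20 | 80% |
| 25% | 20.6 | 0.25 | 75% |
| 40% | 32.9 | 0.32 | 68% |
| 50% | 41.2 | 0.33 | 67% |

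A simulation with 246 completers, 41 of them boys, gave power 0.21. If all 309 were analysed, power would be 0.24 at one-sixth and at most 0.40.

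**The more favourable reading.** If f = 0.15 is the whole-sample effect and boys have none, the effect in girls must be larger, and λ is divided by (1 − p)². Power is then 0.27 at one-sixth (73% missed), 0.42 at 25%, 0.73 at 40% and 0.89 at 50%. A 1-df contrast of the pooled add-ons against control reaches 0.26 at one-sixth on the first reading and 0.35 on this one.

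**The pooled test in the same situation.** Planned effect in girls, none in one-sixth boys: λ ≈ 12.35 × (5/6)² = 8.58, power about 0.74. The pooled test would usually be positive while the gender test usually stays silent.

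**What baseline adjustment gains.** The residual variance falls from 2(1 − ρ) = 1.8 for change scores to 1 − ρ² = 0.99. At one-sixth boys (13.7 per arm), the 95% half-width for one add-on minus ProYouth in boys is:
- change scores: 1.96 × √1.8 × √(2/13.7) = 1.00 SD
- baseline-adjusted: 1.96 × √0.99 × √(2/13.7) = 0.74 SD

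Interaction λ rises to 1.72 × 1.8/0.99 = 3.12, which gives power of about 0.33. The ratio of the half-widths is √((1 + ρ)/2): 0.74 at ρ = 0.1, but 0.87 at ρ = 0.5. The gain is therefore smaller if the true correlation is higher than planned.

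**The case against.** The strongest reply is that the article promises no confirmatory answer for boys. The Background says only that several challenges will be addressed, the Discussion credits inclusion, and the objectives concern the enhanced versions against ProYouth alone. The article does not say that a non-significant interaction will be taken as efficacy in boys. Low interaction power is common to most trials, and the male share is an assumption: the cited prevalences describe full and sub-threshold disorders in young adults, not pupils from age 12 selected by weight concerns or weekly symptoms. The fix also leaves the boys' half-width (0.74 SD) wider than the planned effect (0.64 SD).

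Much of this stands. There is no contradiction in the text, and low power by itself breaches no stated figure. The miss rate must be given as a range with its conditions. What remains is that the named method is less precise than one available from the same data, and that the article does not mark its result as exploratory.

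A reader might go further and infer that age is ignored altogether, or that the trial answers neither evidence gap. The documents do not support either inference. An age analysis may be set out in a full protocol or SAP that is not shown, so its absence from an article is no finding. The trial will also yield data on pupils from age 12 and on boys, which is all that the article claims.

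**Conclusion.** The point holds for gender only, and as a matter of method and interpretation. If girls have the planned effect, boys none, and 247 complete, the three-way test detects the difference with power of at most 0.33 at any gender mix; it misses it in 67% to 90% of trials for male shares from 50% down to 5%. One-sixth boys, hence 80%, is an assumption. Under the whole-sample reading of f = 0.15 the test is adequate only if boys approach half the sample, well above what the cited prevalences suggest. A non-significant gender interaction should therefore not be used to carry a pooled result over to boys. The primary analysis and its conclusion are not affected.

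**What to change.** In Statistical analysis, replace the multifactor ANOVA for gender by one model for the 6-week ChEDE-Q global score with arm, baseline score, gender and arm by gender. From it, report each add-on minus ProYouth with a 95% confidence interval for girls and for boys. Label the analysis exploratory, as the Discussion already does for the comparison of the two add-ons, and state that any conclusion on boys rests on their own interval and not on the interaction p-value. An age term could be added to the same model but is optional.

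This uses data already collected and needs no extra participants; the cost is a change of wording and a few more estimates. The drawback is that the boys' interval will remain visibly wide, so what the trial can say about efficacy in males becomes more modest.
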